### **Research plan and methodology**

#### **Study Design**

This is a two-arm parallel randomized controlled trial.

#### **Setting and Participants**

This study will be conducted in the Department of Paediatrics & Adolescent Medicine, Tseung Kwan O Hospital. The unit admit general pediatric patients. Venipuncture will be performed by a doctor or trained phlebotomist and will be conducted in the treatment room. No local analgesics will be applied before the procedure. Usually at least one staff (nurse or health care assistants) will assist in the procedure (by saying comfort words and restraining the child from vigorous movement). Parents will wait outside the treatment room during the procedures.

Eligible pediatric patients: (1) aged between 4 and 12 years; (2) scheduled to undergo venipuncture; and (3) able to communicate in Cantonese and follow instructions. Potential participants will be excluded according to the following: (1) identified cognitive and learning problems in their medical record; (2) sensory impairment to pain (such as spinal bifida); (3) identified contact precautions; and (4) previous history of seizures or motion sickness. This study selects 4–12 year-old patients because they experience high level of distress in

venipuncture procedure [4], and distraction is efficacious in this age group [14]. Younger patients will not be included because of their possible limited cognitive and verbal capacity to respond to the questionnaires.

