## Secondary outcomes

**Visual analogue scale for anxiety:** A visual analogue scale (VAS) for anxiety will be used to assess the anxiety levels of children aged 4–7 years old. The VAS is a 10 cm horizontal line marked with the words "not worried" (low score) at one end and "very worried" (high score) at the other, with different facial expressions drawn along the line. Children aged between 4 and 7 will be asked to indicate their levels of anxiety by moving a pointer over the line, with higher scores indicating greater anxiety. The VAS is a widely used scale which is reliable and valid for measuring the subjective feelings of children [40]. It has been used previously by PI to assess the anxiety level of children undergoing medical procedures [41].

**State anxiety scale for children:** The short form of the Chinese version of the State Anxiety Scale for Children (CSAS-C) will be used to measure the anxiety levels of children aged 8-12 [42]. The CSAS-C is a 3-point Likert scale with total scores ranging from 10 to 30. Higher scores indicate greater anxiety levels [41]. The psychometric properties of the short form has been tested and found to correlate strongly with the full form ( $r = 0.92$ ). It has good internal consistency ( $r = 0.83$ ) and convergent validity that differentiate the anxiety state of children under various situations [43]. The PI has previously used it to assess the anxiety level of children undergoing medical procedures with Cronbach's alpha 0.80 to 0.88 [41].

**Heart rate:** The heart rate of the children will be measured by a standard automatic heart rate monitoring machine (available in the study institution) to assess the physiological responses of children. Heart rate is considered to be objective and definitive in indirectly assessing physiological responses of pain and anxiety of children [23-24].

**Salivary cortisol assay:** Saliva cortisol assay will be used as to assess the stress levels of the children [44]. The trained RA will collect saliva samples from the patients using the Salivette sampling devices, according to the manufacturer's instructions at 10 min prior and 30 min after the venipuncture procedures [44]. Collected saliva samples will be frozen at  $-80^{\circ}\text{C}$

until further processing and analysis. Cortisol levels in the saliva samples will be measured using an enzyme-linked immunoassay kit (Salimetrics, PA, USA), according to the manufacturer's instructions.

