#### **Data Collection Procedures**

Children requiring venipuncture will be identified by the nurse in the pediatric unit. If the children meet the inclusion criteria for recruitment, the nurse will refer the children and their accompanying parents/ legal guardians to the RA in the treatment room, who will give them an information sheet, explain the study and show the IVR equipment. If they agree to participate, written informed consent from the accompany parents/ legal guardians and assent from the children will be obtained. The RA will then acquire socio-demographics information from the parents/ legal guardians and clinical characteristics of the children from medical record before randomization. According to the subject allocation scheme, children in the control group will receive standard care, whereas those in the intervention group will additionally receive IVR intervention.

Participants will be assessed:10 minutes prior to the procedure (T0), during the procedure when the needle insert to the skin (T1), immediately after the procedure indicate by application of band aid to the venipuncture site (T2), and 30 minutes after the procedure (T3). At T0, a set of baseline data - saliva sample for a measure of cortisol, FPS-R, VAS for anxiety, CSAS-C, and heart rate - will be collected from the patients by the RA. At T1, heart rate will be obtained. At T2, FPS-R, VAS for anxiety, CSAS-C and heart rate will be obtained from children. At the same time, the RA will record the length of procedure and invite the health care providers involved to fill in the staff satisfaction scale. At T3, saliva sample for a measure of cortisol, FPS-R, VAS for anxiety, CSAS-C, and heart rate will be obtained from patients again. Please refer to table 1 and figure 1.

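### Recording the clock time of saliva samples and recent steroid or beta-agonist use would cheaply reduce noise in the cortisol and heart-rate comparisons (minor, secondary endpoints only)

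*Protocol*

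**What the plan says.** - **Population and eligibility** (Protocol, Setting and Participants): "The unit admit general pediatric patients". There are three inclusion and four exclusion criteria. The exclusions concern cognitive or learning problems, impaired pain sensation, and finally "identified contact precautions; and (4) previous history of seizures or motion sickness". None refers to medication or adrenal disease.
- **Cortisol** (Secondary outcomes): "Saliva cortisol assay will be used as to assess the stress levels of the children". Sampling follows the manufacturer's "instructions at 10 min prior and 30 min after the venipuncture procedures". The timing is relative to the procedure; no hour of day is fixed, and recording it is not mentioned.
- **Heart rate** (Secondary outcomes): "Heart rate is considered to be objective and definitive in indirectly assessing physiological responses of pain and anxiety of children". It is measured at T0, T1, T2 and T3.
- **Baseline data** (Data Collection Procedures): the research assistant obtains "clinical characteristics of the children from medical record before randomization", with no list of fields. Cortisol and heart rate are both measured at T0.
- **Randomisation**: 1:1, concealed until baseline data are in, stratified by age group only.
- **Data analysis**: intention to treat, with GEE comparing the arms across time points. No covariate is named.

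**The concern.** Hypothesis (1) names stress alongside pain and anxiety, and cortisol is the measure the Protocol assigns to stress, with two samples per child. Participants, research assistant and providers will not be blinded, so cortisol and heart rate are the secondary outcomes least exposed to reporting bias. It is worth keeping them readable.

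Both can move for reasons unrelated to the procedure. As general pharmacology and physiology, not taken from the documents: a systemic corticosteroid can blunt a child's own cortisol response or be picked up by an assay, a beta-agonist can raise heart rate, and cortisol varies over the day. Children on such drugs are eligible, and venipuncture may fall at any hour. If neither the drugs nor the hour is recorded, this variation stays in the error term, and children who cannot respond pull the estimated effect towards zero.

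A SAP may well choose covariates and sensitivity analyses, but it can use only data that were collected. The point for the Protocol is therefore data capture.

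**Working it through.** **1. The plan's own figure.** The sample size rests on FPS-R alone: difference 0.8, SD 1.84, 80% power, two-sided 5%. A two-sample t-test needs 84.01 per group, so 85. Then 2 × 85 = 170; 170 / 0.85 = 200; 200 / 0.80 = 250. The stated figures reproduce. None depends on cortisol or heart rate.

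**2. Bias or noise?** A null simulation used 85 per arm, 20% medicated children and sampling spread uniformly over 12 hours, both independent of arm (all assumed). Type I error was 4.9% and the mean between-arm difference about 0. The contamination does not create a difference between arms. What remains is lost precision and dilution.

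**3. Size for steroid use.** The documents give no prevalence of steroid use, no cortisol SD and no power for cortisol, so everything here is assumed. Let a fraction f of children take steroids, show no IVR effect and have r times the SD of the others. Let power be 80% in a sample without steroid users, so the noncentrality is 1.96 + 0.84 = 2.80. Relative to that sample it is multiplied by

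- all children analysed: k = (1 − f) / √((1 − f) + f r²)
- steroid users left out: k = √(1 − f)

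and power = Φ(2.80 k − 1.96).

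Worked for f = 10%:
- r = 0.5: k = 0.9 / √0.925 = 0.936, power 75%
- r = 1: k = 0.9, power 71%
- r = 2: k = 0.9 / √1.3 = 0.789, power 60%
- left out: k = √0.9 = 0.949, power 76%

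| f | r = 0.5 | r = 1 | r = 2 | r = 3 | left out |
|---|---|---|---|---|---|
| 5% | 77% | 76% | 70% | 61% | 78% |
| 10% | 75% | 71% | 60% | 47% | 76% |
| 20% | 68% | 61% | 43% | 28% | 71% |

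If steroid simply suppresses cortisol, the affected values should be less variable (r below 1). Leaving those children out then gains at most about 3 points (71% against 68% at f = 20%). The large losses need r of 2 or 3, for example through an assay reading the drug, which the documents do not describe.

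**4. Size for clock time.** Again an illustration, borrowing the FPS-R standardised effect of 0.8 / 1.84 = 0.435 with 85 per arm. If an unrecorded source adds 10%, 25% or 50% to the outcome variance, the effect becomes 0.435 / √1.10, / √1.25 or / √1.50, and power falls from 80.5% to 77%, 71% or 63%. The documents do not say where in this range the trial lies. No separate figure can be given for beta-agonists and heart rate.

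**The case against.** **The design already absorbs much of this.** Both measures have a T0 value and the GEE compares arms over time, so stable differences between children largely drop out of the change. Concealed 1:1 allocation balances the rest in expectation. This stands, and it limits the point to precision. It does not cover a blunted response, a drug effect that changes between T0 and T3, or drift over the sampling interval.

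**The data may be collected anyway.** The clinical characteristics are not itemised and the case-report form is not in the documents, so medication may be among them. The Implementation Protocol also has the research assistant note the time of the first attempt. If that is a clock time, the sampling hour can be approximated from it. This stands in part: the text does not commit to either use, and a stated field settles it.

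**Covariates and sensitivity analyses belong in the SAP.** True of the choice of model, but not of capturing the data it needs.

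**Stronger readings that a reader might infer.** One is that the eligibility criteria are wrong. They are not shown to be: these children can supply valid primary-outcome data, and nothing here calls for excluding them. Another is that the arms would be compared with bias, or that a null cortisol result would be uninterpretable. Randomisation and the simulation speak against the first. The second does not follow from 71% against 76% power, and the Theoretical Frameworks section rests the physiological evidence on heart rate as well as cortisol. A third is that the main cortisol analysis should be restricted to children not on steroids. That sits badly with the stated intention-to-treat principle.

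**Conclusion.** A minor but worthwhile improvement. The Protocol does not specify recording the clock time of saliva samples, recent systemic corticosteroid or beta-agonist use, or adrenal disorder. The cortisol and heart-rate comparisons therefore carry noise and some dilution that could be avoided at little cost and that later analysis cannot remove unless the data exist. There is no systematic bias between arms, and FPS-R and its sample size are untouched.

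The size is unknown. With an assumed 10% of steroid users showing no effect, and 80% power without them, cortisol power ranges from about 75% (r = 0.5) through 71% (r = 1) to 60% (r = 2), against 76% with those children left out. The loss could be negligible or material, depending on a prevalence and an SD ratio that the documents do not give.

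**What to change.** 1. Leave eligibility unchanged.
2. In Data Collection Procedures, add three fields to the record review before randomisation: systemic corticosteroid use within a stated window, known adrenal disorder, and beta-agonist use within a stated window.
3. Record the clock time of each saliva sample.
4. Keep all randomised children in the main cortisol and heart-rate analyses. Adjust the cortisol GEE for clock time of sampling, and let it interact with time point so that drift between T0 and T3 is also covered. Using the T0 clock time keeps the covariate pre-randomisation; the T3 time could shift slightly with arm, since procedure length is itself an outcome.
5. Pre-specify sensitivity analyses, defined from pre-randomisation data only: cortisol without steroid users or children with adrenal disorder, and heart rate without beta-agonist users.

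Cost: a few extra form fields and slightly more analysis. Recruitment, the primary outcome and clinical care do not change.

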#### **Sample size – Patients**

In 2016, about 250 hospitalized patients aged between 4 years to 12 years were admitted to the unit and required venipuncture. Sample size estimation was based on the effect estimated from a previous IVR study using the FPS-R Scale as a primary outcome measure [11]. By using the power analysis software, GPower 3.1, it was estimated that a sample size of 85 participants per group would enable a 2-arm RCT to detect a between-group difference of 0.8 in FPS-R scale with a pooled standard deviation of 1.84 with 80% power at 5% level of significance. Taking into account of up to 15% attrition rate [24], 200 children will be recruited. Furthermore, to account for those who fail in the first attempt of venipuncture, the total sample size is adjusted to 250 children to be recruited with the estimation of 20% of unsuccessful cases in the first attempt. As such, the total recruited number of children will be 250 for the experimental and control groups, with 125 children in each group.

#### ***Health care providers***

About 10 health-care providers involved in venipuncture procedures (e.g. doctors, phlebotomist, and health care assistants) will be invited to assess their satisfaction for the procedures.

#### **Randomization**

Eligible participants will be randomly assigned in a 1:1 ratio to the intervention group who will receive the IVR intervention or a control group that will receive standard care only using stratified permuted block randomization with a block size of 10 to maintain a good balance of participants between the two groups throughout the subject recruitment period. Randomization will be stratified by age group (4–7; 8–12 years old) in equal numbers.

According to Piaget’s theory, children from 4 years to 7 years of age belong to the same pre-operational stage, whereas those in the age range 8–12 years belong to the concrete operational stage [31]. Children in different stages differently perceive information and pain stimuli sensitivity [32].

A sequence of grouping identifiers (I=intervention group or C=control group) will be prepared in advance by an independent statistician, using computer-generated random codes for each of the two strata of age group. The group identifiers for each age group will then be put in serially numbered sealed opaque envelopes according to the underlying random sequence list by the statistician. The group allocation of the patients will be assigned according their ages, sequence of enrolment in the study, and the group identifier contained in the corresponding numbered envelopes. Group allocation will be concealed from the research assistant (RA), ward staff, child, and parents/ legal guardians until consent and baseline assessment data has been obtained. Given the nature of the intervention, blinding of participants, RA, and health care provider will be difficult. Nevertheless, the lack of blinding will not necessarily contribute to a source of bias because children are unlikely to change their behavior even when they know they are participating in a certain intervention [33].

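### A single block size of 10 is printed in the protocol of an open, single-site trial; an RA who keeps counts could know about 16% of allocations before consent and baseline are complete

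*Protocol*

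**What the plan says.** The Protocol, under Randomization, has children "randomly assigned in a 1:1 ratio to the intervention group" or to control, by "stratified permuted block randomization with a block size of 10". It adds: "Randomization will be stratified by age group (4–7; 8–12 years old) in equal numbers". Order of use is also fixed: "The group allocation of the patients will be assigned according their ages, sequence of enrolment in the study", together with the numbered envelope for that stratum.

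The safeguards are in the same section. An independent statistician prepares the sequence by computer, and the group identifiers are "put in serially numbered sealed opaque envelopes according to the underlying random sequence list by the statistician". The protocol also states: "Group allocation will be concealed from the research assistant (RA), ward staff, child, and parents/ legal guardians until consent and baseline assessment data has been" collected. It concedes that "blinding of participants, RA, and health care provider will be difficult".

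Other sections set out who does what. Setting and Participants names one hospital department. Fidelity of the Intervention describes a single RA. Under Data Collection Procedures, a ward nurse identifies eligible children and refers them; the RA then explains the study and shows the equipment. After consent, "The RA will then acquire socio-demographics information from the parents/ legal guardians", and the RA also collects the T0 FPS-R, anxiety ratings, heart rate and saliva. Under Implementation Protocol, the RA instructs the child on the equipment and removes it afterwards.

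**The concern.** The safeguards protect the envelope that is about to be opened. They do not stop anyone from working out its content from those already opened. In a 1:1 block of 10, once five children in a stratum's block have gone to one arm, the rest of that block must go to the other. The person best placed to count is the RA, who handles the headset in the intervention arm and therefore can know which earlier children received it.

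The same RA explains the study and elicits the T0 ratings before the next envelope is opened. Foreknowledge could colour how consent is discussed or how a young child is prompted for baseline pain and anxiety. T0 enters the results: Data analysis compares the groups across time points, and the cost-effectiveness ratio uses change in FPS-R from baseline. Selection on characteristics that are not recorded cannot be reliably adjusted away later.

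The protocol's one comment on bias from lack of blinding concerns the children's own behaviour. It does not address the staff who obtain consent and take ratings.

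**Working it through.** **Inputs.** From Randomization: ratio 1:1, block size 10 (m = 5 per arm), two age strata. From Sample size: 250 children in total. Assumption: the equal-numbers phrase means 125 per stratum, that is, 12 full blocks and half a block each. Assumption: the RA knows or infers the block size, keeps a count per stratum and knows each past allocation.

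**The plan's own figures.** The protocol gives no predictability figure. Its total reproduces: for a difference of 0.8 and SD 1.84, two-sided 5%, exact t-test power is 0.7999 at 84 per group and 0.8046 at 85. Then 170/0.85 = 200 and 200/0.80 = 250.

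**Certain allocations per block.** The k-th allocation from the end of a block is known with probability 2·C(10−k, 5)/C(10, 5), where C(10, 5) = 252:

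| Position from end | Probability known |
|---|---|
| last | 252/252 = 1.000 |
| 2nd last | 112/252 = 0.444 |
| 3rd last | 42/252 = 0.167 |
| 4th last | 12/252 = 0.048 |
| 5th last | 2/252 = 0.008 |

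The sum is 420/252 = 1.667, matching the closed form 2m/(m+1) = 10/6. That is 16.7% of a full block. Nothing is certain in the first five places.

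**Over the trial.** Two strata × 12 full blocks × 1.667 = 40.0; the two half blocks add nothing. So 40/250 = 16.0%. If the strata are unequal the total moves little: at most 25 full blocks fit (for example 120 and 130), giving 25 × 1.667 = 41.7, or 16.7%.

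**Best guess.** Correct guesses per full block are m + (2^10/252 − 1)/2 = 5 + (4.063 − 1)/2 = 6.532, or 65.3%. A half block gives 2.802 of 5. The trial total is 2 × (12 × 6.532 + 2.802) = 162.4 of 250, or 64.9%, against 125 by chance.

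**Effect of varying the block size.** Strata of 125 were simulated (600 replicates). The guesser knows the set of possible sizes, each equally likely, but not the size in use. The mixes are illustrative.

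| Block sizes | Known with certainty | Best-guess hit rate | Guessable with ≥75% probability |
|---|---|---|---|
| 10 only | 16.0% | 65.0% | 23.1% |
| 8, 10, 12 | 1.2% | 64.9% | 20.2% |
| 6, 8, 10, 12 | 0.9% | 65.5% | 19.0% |
| 4, 6, 8 | 2.4% | 67.9% | 34.4% |

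The hit rate barely moves for a simple reason. The best guess is the arm with fewer children so far in that stratum, and this needs the running balance, not the block size. Mixes with small blocks make it worse.

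**The case against.** The strongest reply is that concealment here is already of a standard kind: an independent statistician, a computer-generated list, sealed envelopes, and disclosure only after baseline. Ten is also a fairly large block. By the same formula a block of 4 gives 33.3% certain and a block of 6 gives 25.0%, and here two interleaved strata must be tracked. All of this stands. It limits the concern but does not answer it, because these measures do not act on inference from past allocations.

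Two links are inferred. The protocol does not say that the RA is told the block size, and the listed training does not cover randomization. Equally, nothing withholds the size, and a constant size can be worked out from the recurring balance. That the RA can know every past allocation follows from there being one RA who handles the headsets; it is not stated.

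A reader might infer that the RA could choose whom to approach. Data Collection Procedures does not support that: the nurse identifies and refers children. What remains is how the study is explained and how baseline is elicited. Even there, the FPS-R is the child's own choice of face under a scale protocol described as standardized. A reader might also infer that selection bias is established. It is not: predictability is an opportunity, and the documents give no basis for a size in FPS-R points.

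Finally, the same unblinded RA collects the outcomes at T2 and T3 knowing every child's group. That exposure is larger, and foreknowledge of about one allocation in six adds little to it. This supports a low priority. The route is nonetheless different, since it acts before randomization, and it is cheap to narrow.

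**Conclusion.** The point holds as a low-priority improvement. It is not an error or contradiction in the protocol. With a single printed block size of 10, a counting RA would know about 40 of 250 allocations (16.0%; up to 16.7% if the strata are unequal) before consent and baseline are complete. This rests on the RA knowing or inferring the block size, tracking both strata and knowing all earlier allocations, and on 250 children being enrolled.

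It would be too strong to say that upcoming allocations in general can be predicted. About five in six cannot be known with certainty. The roughly 65% hit rate for best guesses should not be presented as something that varying the block sizes would cure, since it stays near 65%. What can be removed is certain knowledge, the most exploitable part. No statistical analysis plan was at hand, but the block size is printed in the protocol itself.

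**What to change.** Have the independent statistician generate each age stratum's list with randomly varying block sizes, for example 8, 10 and 12, or sizes from 6 to 12. Keep the sizes in a document withheld from the RA and ward staff. In the Randomization section, replace the stated size with a statement that block sizes vary randomly.

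Certain foreknowledge then falls from 16.0% to about 1% (1.2% or 0.9% in the two mixes, that is about 3 or 2 of 250), even if the set of sizes becomes known. The best-guess rate stays near 65%. Lowering that would need the consent and baseline steps to be done by someone who does not see earlier allocations, which is a larger staffing change.

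The sample size is unchanged. The cost is regenerating the list before the first envelope is used, or regenerating the unused envelopes, and at most a few participants of end-of-trial imbalance. An unfinished block of 12 can leave the arms at most 6 apart in a stratum, against at most 5 for a block of 10.

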## 51    **Background of research**

52       Hospitalized children experience pain and anxiety from invasive procedures and/or their  
53    underlying diseases [1]. Venipuncture, a frequently performed needle-related procedure, is  
54    the most frightening experience and a common source of moderate to severe pain for  
55    pediatric patients [1-2]. The pain associated with the procedure is secondary only to the  
56    illness itself [3]. Approximately 83% of children aged 2.5–6 years, 51% of children aged 7–  
57    12 years, and 28% of adolescents (>12 years of age) who underwent venipuncture reported  
58    high levels of distress during the procedure [4]. However, less than 10% of venipuncture  
59    procedures are provided with pain management [2].

60       Inadequate pain management can negatively affect children, parents, and medical  
61    institutions [5-10]. Unmanaged needle-related procedural pain in children is associated with  
62    increased pain and stress during subsequent procedures, fear and avoidance of medical care,  
63    or even the development of needle phobias that persist into adulthood [3, 6-8]. Failure to  
64    manage needle-related pain may increase the manpower, resources, and time required to  
65    complete procedures, consequently reducing health-care providers' satisfaction with respect  
66    to the procedures [5, 10].

67       Pre-procedural local analgesics have been traditionally used to manage needle-related  
68    procedural pain. However, high levels of pain and distress were reported in children even  
69    with pharmacological interventions [11-12]. Thus, clinical guidelines highlight the important  
70    role of non-pharmacological interventions alone or as clinical adjunct in managing procedural  
71    pain [13].

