#### **Intervention: IVR**

In addition to standard care, children in the intervention group will receive IVR intervention through a commercially available VR headset, which can be fitted into majority of commonly available smartphones. Although other latest headsets, such as Oculus Rift or HTC Vive, can provide high quality of immersion experience, they likewise increase the risk

of contact infection and require a high spectrum personal computer to operate. Therefore, these devices will not be used in this study.

With regard to the IVR modules, previous work conducted by lead PI's research team selected five modules for patients. Examples of these modules include interactive games, cartoon animation, and animated scenery. Among these modules, cartoon animation and interactive games were considered interesting by patients and can capture their attention for an extended period of time. For instances, cartoon animation was preferred by young patients, whereas the interactive game was preferred by adolescents; these results concurred with a previous study [25]. An IVR module that presents procedural information through a customized and child-friendly design more effectively mitigates pain and distress than that with off-the-shelf content [18, 30, 34]. However, these freely downloaded IVR modules that were developed in Western countries with English as the medium may not be completely appropriate for pediatric patients in Hong Kong. In the proposed study, IVR modules have been designed on the basis of suggestions to use age-appropriate modules for patients [16-17] and the experiences of the lead PI, who has successfully developed six cartoon animations in previous studies [35]. The lead PI has produced two developmentally appropriate IVR modules: One for 4–7 year-old children and one for 8–12 year-old children. The two modules share the following common characteristics with those used in previous studies: (1) a wide range of visual and auditory stimuli [11, 23-24]; (2) requiring minimum movement of head and hand to allow the procedures to proceed unhindered [36]; and (3) provision of procedural information. Both modules have been validated by an expert panel and used in pediatric cancer patients during venipuncture.

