## **Data analysis**

IBM SPSS 24 will be used for data analysis. Continuous demographic and clinical variables will be presented as their means and standard deviations, whereas categorical data (e.g. sex) will be presented in frequencies and percentages, as appropriate. The intention-to-treat principle will be adopted for the outcome comparisons between the intervention and control groups. The generalized estimating equations (GEE) model will be used to compare each of the outcome measures across the time points between the two groups. GEE model can account for intra-correlated repeated measures data and produce unbiased estimates even if there are missing data, provided that the data are missing at completely random. Cohen's d values will be calculated to estimate the effect sizes of the IVR intervention on the outcome variables. All statistical analyses are two-sided and level of significance will be set at 0.05.

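### The stated GEE leaves out the age stratum used in randomisation; if age is prognostic, standard errors are conservative by an amount the protocol does not allow to be fixed (0% to about 19%)

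*Protocol*

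**What the plan says.** Protocol, Randomization: allocation is 1:1 in permuted blocks of 10, with a separate random list for each of two age groups. "Randomization will be stratified by age group (4–7; 8–12 years old) in equal numbers". The ground given is that children in the two developmental stages take in information differently and differ in pain sensitivity, so the protocol itself treats age group as prognostic.

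Protocol, Data analysis: "The generalized estimating equations (GEE) model will be used to compare each of the outcome measures across the time points between the two groups". The paragraph also fixes intention to treat, Cohen's d and the two-sided 5% level. It names neither age stratum nor any other covariate, and it does not say that the model is unadjusted.

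Two other features vary with the stratum. Under Intervention: IVR, there are two modules: "One for 4–7 year-old children and one for 8–12 year-old children". Under Secondary outcomes, anxiety is measured by a VAS at ages 4–7 and by the CSAS-C at ages 8–12.

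The only age gradient in the document is in Background of research, where high distress is reported as follows: "Approximately 83% of children aged 2.5–6 years, 51% of children aged" 7–12. No FPS-R mean or SD by age is given.

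**The concern.** Stratified blocks remove the difference between age groups from the comparison of arms. A model without the stratum still counts that difference as residual variation. It therefore reports a standard error larger than the true sampling variability of the treatment estimate. Robust (sandwich) standard errors do not cure this, because they are built from the same residuals.

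At stake is precision: confidence intervals wider than they need be, p-values that are conservative, and some power given up. There is also a choice left open. If the model is not fixed in advance, adjusted and unadjusted results could both be computed and one preferred afterwards.

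**Working it through.** **1. The protocol's own figure.** Inputs from Sample size – Patients: "a between-group difference of 0.8 in FPS-R scale", "with a pooled standard deviation of 1.84", "with 80% power at 5% level of significance". Data analysis confirms a two-sided test.

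- Normal approximation: n = 2 × (1.960 + 0.842)² × 1.84² / 0.8² = 83.04, so 84 per group.
- Two-sample t-test (noncentral t): 85 per group, power 80.5%.
- Inflation: 170/0.85 = 200; 200/0.80 = 250.

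The stated 85, 200 and 250 all reproduce.

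**2. Cost of omitting the stratum, single time point.** Assumptions: strata 50:50, total SD 1.84, mean FPS-R difference between strata D (not given; taken as 0 to 2 points).

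- Share of variance due to stratum: R² = (D²/4) / 1.84²
- Reported SE without the stratum: 1.84 × √(2/85) = 0.2822
- True SE under stratified allocation: 0.2822 × √(1 − R²)
- SE ratio: 1/√(1 − R²)
- Unadjusted power: Φ((0.8 − 1.96 × 0.2822) / true SE)
- Adjusted power: Φ(0.8 / true SE − 1.96)
- Actual type I error, unadjusted: 2 × (1 − Φ(1.96 × SE ratio))

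| D | R² | SE ratio | Power unadjusted | Power adjusted | Type I error unadjusted |
|---|---|---|---|---|---|
| 0 | 0 | 1.000 | 80.9% | 80.9% | 5.0% |
| 0.5 | 0.018 | 1.009 | 81.1% | 81.6% | 4.8% |
| 1 | 0.074 | 1.039 | 81.8% | 83.8% | 4.2% |
| 1.5 | 0.166 | 1.095 | 83.1% | 87.4% | 3.2% |
| 2 | 0.295 | 1.191 | 85.1% | 92.2% | 2.0% |

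**3. The distress gradient as a rough proxy.** With 83% and 51%, the mean is 0.67. R² = (0.32²/4) / (0.67 × 0.33) = 0.0256/0.2211 = 0.116.

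- SE ratio: 1/√0.884 = 1.063; true SE: 0.2822/1.063 = 0.2654.
- Unadjusted power: Φ((0.8 − 0.5532)/0.2654) = Φ(0.93) = 82%.
- Adjusted power: Φ(3.01 − 1.96) = Φ(1.05) = 85%.
- Type I error, unadjusted: about 3.7%.

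**4. Group-by-time contrast.** Simulation: 20,000 runs, 42 children per arm per stratum, robust SEs, within-child correlation assumed 0.5. Here 1.84 is the within-stratum SD, so ratios differ slightly from step 2.

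| Age difference in FPS-R | SE ratio, post-procedure score | SE ratio, change from baseline |
|---|---|---|
| 1 point, constant over time | 1.04 | 1.003 |
| 2 points, constant over time | 1.14 | 1.003 |
| 1 point at baseline, 2 points after | 1.14 | 1.04 |

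The treatment estimate was identical with and without the stratum term in every run. With no treatment effect and a constant 2-point age difference, the post-procedure test rejected in 2.9% of runs unadjusted and 5.5% adjusted.

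**5. What stratum-specific results could show.** With 85/2 = 42.5 evaluable children per arm per stratum:

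- SE within one stratum: 1.84 × √(2/42.5) = 0.399; power for 0.8 points: Φ(0.8/0.399 − 1.96) = 52%.
- Interaction detectable with 80% power: 2.80 × 1.84 × √(4/42.5) = 1.58 points, about twice the target effect.

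**The case against.** **Silence is not a decision.** The analysis paragraph does not declare an unadjusted model, and covariates are often left to an SAP, which was not available here. This stands as a limit: the protocol cannot be said to reject adjustment. But it does state a model, and run as written that model omits a factor that the design uses and justifies as prognostic.

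**The size is not known.** The proxy is a yes/no distress measure, not FPS-R, and its bands (2.5–6 and 7–12) are not the trial's strata. This stands in full; about 6% is an illustration.

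**A constant age difference cancels in a group-by-time contrast.** True, as step 4 shows. It is not certain to apply. FPS-R at T0 is taken before the needle, whereas the protocol expects ages to differ in sensitivity to painful stimuli, so strata may also differ in change. Length of procedure and staff satisfaction have no baseline (Data Collection Procedures), so nothing cancels for them.

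**Three stronger readings that a reader might infer are not supported.**

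- *That adjustment raises power from 80% to 85%, or that the benefit of stratifying is lost.* Stratified allocation lowers the true variance whether or not the model adjusts. Under the proxy the unadjusted test already has about 82% power, and balance between arms is kept.
- *That every outcome is affected.* Each anxiety scale is used in one stratum only. The stratum is constant within it, so no SE is inflated and no stratum term can be estimated.
- *That omitting the stratum blurs the effects of the two modules.* Module is fully aliased with age, so neither a stratum term nor an interaction separates them. The hypotheses concern IVR against standard care, and the pooled estimate is a valid average for age-appropriate IVR.

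**Conclusion.** The point holds in a limited form. The trial randomises within age strata for a stated prognostic reason, and the stated GEE does not carry the stratum. If age is prognostic for the analysed contrast, the model's standard errors are conservative. The linear treatment estimate is not biased, false positives do not rise, and 85 per arm suffices with or without adjustment.

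The range of 0% to about 19% rests on an assumed FPS-R difference of 0 to 2 points, equal strata, a total SD of 1.84 and a single-time-point comparison. The protocol does not say whether its SD of 1.84 is within or across age groups. This is a modest loss of precision that is free to avoid, not a threat to validity. The omission from the stated model is clear; its size is uncertain.

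**What to change.** In Data analysis, state the following before any comparison by arm:

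- **Outcomes measured in both strata** (FPS-R, heart rate, salivary cortisol, length of procedure, staff satisfaction): include age stratum (4–7; 8–12) as a fixed effect. Where the outcome is repeated, add stratum-by-time, so that an age difference in change is also removed.
- **Anxiety:** analyse the VAS in ages 4–7 and the CSAS-C in ages 8–12 separately.
- **Exploratory only:** for FPS-R, report the arm effect within each stratum and the arm-by-stratum interaction. Say that power within a stratum is about 52% for 0.8 points, and that a difference between strata cannot be attributed to a module.

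The cost is one or two model terms and one extra table. Age group is already recorded for randomisation, so no new data and no change in sample size are needed. If an SAP already contains these terms, a cross-reference is enough.
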